### Data management and ethics

Data will be handled strictly confidentially. Data will be stored in the storage environment of the universities Computing Centre in Leiden. Leiden University treats information security in accordance with the International Security Code. Personal information is processed in accordance with the Dutch Personal Information Protection Act which is based on European legislation. The personal data will be handled according to the Dutch Personal Data Protection Act. A separate subject identification code list will be used to link the data and biological specimen to the subject. There will be no personal identification of subjects in scientific communications. We currently do not have ethical permission for data sharing. Access to the final trial dataset will be limited to the formal research team, including principal investigators, post-docs and PhD-students. All members of the research team signed a confidentiality agreement. The L-CID trial is embedded in the larger national Consortium on Individual Development (CID), which unites developmental researchers from seven different universities. For advice on and supervision of the research program, CID composed an international scientific advisory board and a supervisory board to whom our research team reports at least annually.

The research protocol received ethical approval by the Central Committee on Research Involving Human Subjects in the Netherlands (CCMO; NL49069.000.14). Written informed consent for all aspects of the study was obtained from the parents/legal guardians of the twins before the first baseline assessment. Participants were reminded that participating in the trial is voluntary, that they can withdraw from the trial at any time, without consequences and that their data are stored anonymously and securely. All consent forms and related documentation given to the participants were approved by the CCMO and can be requested from the authors. Information for the participants includes the name and contact information of an independent expert (a MD and professor in child and adolescent psychiatry) who will be available during the trial for questions from participants.

The VIPP-SD has been used in twelve previous RCT’s, including in more vulnerable populations [20], and there are no reported risks associated with the intervention. Therefore, there are no criteria for discontinuing the intervention, except on the basis of participants’ own requests. Concomitant care during the trial is not prohibited, but we will use an inventory about previous experiences with video-feedback or other types of preventive care, such as parent training or well-baby clinics. Trial results will be communicated to participants using newsletters about the trial and to professionals in the form of journal articles and scientific conferences. Authorships for journal articles will be determined based on the APA-guidelines and recommendations from the International Committee of Medical Journal Editors. The trial is registered in the Netherlands Trial Registry (NTR; Trial ID: NRT5312, Date registered: July 20, 2015). Any protocol modifications or plans for ancillary studies will be reported to the NTR, CCMO and this journal, and additional informed consent will be obtained from participants.

## Discussion

This study protocol presents the research design of a randomized controlled trial testing the efficacy of a Video-feedback Intervention to promote Positive Parenting and Sensitive Discipline in a twin sample (VIPP-Twins). It is hypothesized that the parenting intervention will enhance parental sensitivity and sensitive discipline strategies and in turn, positively affect children’s developmental outcomes, specifically social competence and behavioral control. In addition, we aim to test the differential susceptibility theory to examine differential efficacy of the intervention based on genetic make-up or temperament for both parents and children. We expect that parents and children with susceptible genotypes [6] or reactive temperaments will profit most from the intervention.

### Strengths and limitations

An important strength of the study is that the intervention program VIPP-SD has a sound theoretical basis in attachment theory as well as coercion theory [19]. In addition, several previous randomized trials have found empirical evidence for the efficacy of the original version of the VIPP and for several adaptations of the program [20]. Therefore, we have a clear hypothesis about the efficacy of the program, and we can now fill in the gap that exists in knowledge of moderating and mediating factors in the program’s effectiveness.

The random assignment of families to the experimental or control condition is the most important strength of the study design. Random assignment of families to the experimental condition reduces potential gene-environment correlations, and opens the way to test the true moderating effect of participants’ characteristics on intervention efficacy. Because of the longitudinal design of the study with multiple follow-up measures, we can test both short-term and long-term effects of the intervention program. Intervention effects are not only measured on the behavioral level, but also on the hormonal and neural level. Information about intervention effects on neurobiological levels of functioning may explain the long lasting intervention behavioral effects that have previously been documented [10]. A final strength of the study concerns the observational and ambulatory measures, which reduce possible reporter bias related to self-report questionnaire studies.

The study has some limitations that should be noted. First, the large sample size demands multiple interveners, which may lead to divergences in program implementation. However, given the extensive training of interveners, the use of a standardized manual, and frequent supervision, we expect high treatment fidelity. A possible limitation in examining differential susceptibility to intervention effects and the mediators for change in child outcomes is the twin sample. Twin families may be different from families with singletons on several aspects, which may decrease the generalizability of the findings (but see: [46, 47]). The twin sample however also provides the opportunity to test for differential susceptibility within families and for genetic modelling of intervention effects.

In conclusion, the current study will evaluate the effects of a video-feedback intervention in a preschooler twin sample. Results of the study will provide insights in the efficacy of the VIPP-Twins and possible moderators and mediators of program efficacy resulting in an experimental test of the differential susceptibility theory.

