#### Randomization

Randomization to the VIPP-Twins or control condition is done at the family level in a ratio of 2:3, using a computer-generated blocked randomization sequence, with a block size of 19 families based on timing of the intervention and stratified by twin gender. Assignment of participants is performed by an independent researcher who is not involved in data collection or coding. Allocation will be performed after the second pretest, right before the start of the intervention, in order to prevent selective attrition. Researchers, interveners and participants are blinded to assignment before, but not after, randomization, because of the open-label design. To minimize bias based on knowledge about allocation of participants, coders and research assistants who carry out the post-intervention home-visits and laboratory sessions are blind to treatment allocation.

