### Sample size and power

A meta-analysis on the effects of VIPP-SD on caregiver sensitivity indicates a combined effect size of d = 0.47 [20]. For our primary aim, testing the effect of VIPP-Twins on parental sensitivity and sensitive discipline with a repeated measures analyses with α = .05 and a sample size of 225 families (including 450 children), the power is > 90 % (repeated measures ANOVA within-between interaction, G*Power 3.1.9.2). For our secondary aim (main effects on children’s social competence and behavioral control), the power of the multilevel analysis is > 90 %. For the third and fourth aims, testing moderator effects, the power is > 80 %. For the fifth aim, testing mediating mechanisms, the power is > 90 %.

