### Intervention

#### VIPP-SD

The experimental group (40 % of the sample, randomly selected) will receive the Video-feedback Intervention to promote Positive Parenting and Sensitive Discipline - Twins (VIPP-Twins) between the second and third assessment. The VIPP-SD consists of five biweekly sessions in which families are visited at home by a female intervener. All interveners are extensively trained in implementing the intervention by using a standardized manual describing the structure, themes, tips, and exercises for parent and children for each session (manual VIPP-SD version 3.0; [25]). Every session starts with videotaping approximately 15 minutes of standardized parent-child interactions, such as playing or reading a book together [4]. Between sessions, the intervener prepares comments on the child’s or parent’s behavior based on the theme of the next session and selects illustrating video fragments. In the next session, after new video material is collected, the intervener reviews the video of the previous session with the parent and gives video feedback on the chosen video fragments. During this feedback period, the intervener focuses on positive and successful interaction moments and indicates when positive parenting is effective. The parent is explicitly acknowledged as the expert on her own child. The first four intervention sessions each have their own themes with respect to sensitivity and sensitive discipline [19].

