### Statistical analyses

Initial data analysis with data inspection steps will be carried out after the research plan and data collection have been finished but before formal statistical analyses are conducted [42]. We will use double data entry for approximately 20 % of the cases and apply range checks for data values, to promote data quality. It will be tested whether missing data are completely at random, at random, or not at random [43], and multiple imputation procedures will be followed to impute missing data. Data transformation will be applied when necessary to approach normal distribution of data points [44]. To avoid any inflation of statistical tests, we are not planning to examine any interim data-sets.

The overall aim of the study is to estimate the effect of the VIPP-Twins. For all aims, the effect of the VIPP-Twins compared to the control condition will be analyzed using intent to treat analyses. For the primary aim, we propose a repeated measures model to estimate the intervention effect on parental sensitivity and sensitive discipline with experimental condition as between subjects factor and assessment time-point as within subjects factor. The regression coefficient of the interaction between condition and time-point estimates differential changes between the intervention and control groups in parental sensitivity and sensitive discipline over time.

Our secondary aim is to examine the effect of the intervention on children’s levels of behavioral control and social competence. In the current study design, twins are nested within families. Depending on the intraclass correlation (ICC) we will use a multilevel approach with three levels (time-point, child, family) or a repeated measures ANOVA with aggregate scores for the twins within families for analyses with child outcomes. Behavioral control and social competence are included in the analyses using aggregated scores across the different measures.

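### The primary and child-outcome models have no intervener term; if families of one intervener are alike, the standard error of the condition-by-time effect is understated

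*Protocol article*

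**What the plan says.** - **Allocation (Randomization).** It is "done at the family level in a ratio of 2:3", which gives 90 intervention and 135 control families out of 225.
- **Delivery (Intervention, VIPP-SD).** The programme is "five biweekly sessions in which families are visited at home by a female intervener". The Control condition section gives control families six phone calls from a research assistant and no visits.
- **Interveners (Strengths and limitations).** The article notes that "the large sample size demands multiple interveners, which may lead to divergences in program implementation". Its answer is training, a standard manual and supervision, from which it expects high fidelity.
- **Models (Statistical analyses).** The primary model is a repeated measures model "with experimental condition as between subjects factor and assessment time-point as within subjects factor". The multilevel option for child outcomes has three levels: time-point, child and family. The alternative is a repeated measures ANOVA on scores aggregated over the twins. None of these has an intervener term.
- **Power (Sample size and power).** The meta-analysis used "indicates a combined effect size of d = 0.47". Power for the primary aim is put above 90% "with α = .05 and a sample size of 225 families", from a G*Power within-between interaction that treats families as independent.

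**The concern.** Families are randomised one by one, but those in one arm then receive the programme from a shared set of people. This is a partially nested design. If some interveners achieve more than others, the outcomes of families with the same intervener are correlated, and 90 such families carry less information about the programme than 90 independent ones.

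Adjusting for baseline does not remove this. Interveners start work after both pretests, so any difference between them falls on the condition-by-time term, which is the treatment estimate. Training and supervision may make the differences smaller, but they do not correct the standard error for what remains.

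The article deals with one source of clustering (twins within families) in its models. It names a second source as a limitation and leaves it out of them. At stake are the width of the intervals and the p-values for the primary aim and for the main intervention effects on child outcomes.

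**Working it through.** **Inputs from the article:** 225 families, 2:3 allocation (90 and 135), α = .05 (taken as two-sided), d = 0.47.

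**Assumptions, because the article gives no figures:** k = 5 to 10 interveners with equal caseloads m = 90/k (18 to 9 families), and intervener ICC .02 to .05. A wider range is shown as well. Clustering is placed in the intervention arm only.

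**1. The stated power.** With f = 0.47 × √(.4 × .6) = .230, two time-points and zero correlation between repeated measures, λ = .230² × 225 × 2 = 23.86 (unrounded f), which gives power .998. Using 2 to 4 time-points and correlations of 0 to .5 gives .998 or more throughout. A plain comparison of 90 with 135 families gives .47/√(1/90 + 1/135) = 3.45 and power .93. The figure of more than 90% is reproduced either way, with families treated as independent.

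**2. Variance with clustering.** At unit variance the stated model uses 1/90 + 1/135 = .01852. Clustering multiplies the first term by DE = 1 + (m − 1) × ICC. The first term is 60% of the sum, so the variance ratio is R = 0.6 × DE + 0.4.

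**3. True type I error of the unadjusted test:** 2 × [1 − Φ(1.96/√R)].

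- k = 10, ICC .02: DE = 1 + 8 × .02 = 1.16; R = 1.096; √R = 1.047; error .061.
- k = 6, ICC .05: DE = 1 + 14 × .05 = 1.70; R = 1.42; √R = 1.192; error .100.
- k = 5, ICC .05: DE = 1 + 17 × .05 = 1.85; R = 1.51; √R = 1.229; error .111.

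| Interveners | ICC 0 | .01 | .02 | .05 | .10 |
|---|---|---|---|---|---|
| 4 | 5.0% | 6.5% | 8.1% | 12.7% | 19.5% |
| 5 | 5.0% | 6.2% | 7.4% | 11.1% | 16.8% |
| 6 | 5.0% | 6.0% | 7.0% | 10.0% | 14.9% |
| 10 | 5.0% | 5.6% | 6.1% | 7.8% | 10.7% |
| 15 | 5.0% | 5.4% | 5.7% | 6.8% | 8.6% |

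Simulation (20,000 trials per setting) agrees. For 6 interveners it gives 4.7%, 7.1%, 9.6% and 15.0% at ICC 0, .02, .05 and .10.

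**4. Effect on power.** Dividing the smallest noncentrality in step 1 by the largest main ratio gives 23.86/1.51 = 15.80, and power .977. For 5 interveners and ICC .05, a Satterthwaite approximation with a = 1.85/90 and b = 1/135 gives (a + b)²/(a²/4 + b²/134) = 7.4 degrees of freedom. Even with these, power at λ = 15.80 is about .93. By the plan's own method it stays above 90%.

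**The case against.** **The article does not say that interveners will differ.** It says that divergence may occur and that it expects high fidelity. This stands: a positive ICC is not established, so the finding is conditional. At ICC .01 with 10 or more interveners the error is only about 5.4% to 5.6%.

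**Under a strict null there is nothing to cluster.** Post-test assessors and coders are blind to allocation, so interveners do not rate outcomes. If the programme does nothing in anyone's hands, the error stays at 5%. It also does so if the conclusion is limited to these interveners. Inflation needs intervener effects that vary around zero and a conclusion about interveners in general. This stands as a condition, but the article's aim is to judge the programme, which is the wider target.

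**A condensed article may leave random effects to the analysis plan.** This carries some weight, and an unseen plan may add the term. But the article is not silent: it lists the model's factors and levels, and names the source of clustering that they omit.

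**Partial nesting is not certain.** The Aims and hypotheses section describes the control contacts as being with the interveners, while the Control condition section names a research assistant. The calculation follows the latter.

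A reader might infer three stronger points, and the documents support none of them:
- *The type I error is inflated as a matter of fact.* It depends on two figures that are not given.
- *The error favours the intervention.* The estimate is unbiased and the test two-sided, so false positives fall in both directions.
- *The power claim fails.* On the plain two-group basis, power at 5 interveners and ICC .05 falls from .93 to .80 (normal approximation) or .68 (7.4 degrees of freedom). That is not the method the article used.

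**Conclusion.** The concern holds in conditional form. The stated models treat intervention families as independent although they share interveners. If the intervener ICC is above 0 and the conclusion is meant for the programme, the standard error is too small: by a factor of 1.05 to 1.23 for 5 to 10 interveners and ICC .02 to .05, with a type I error of about 6% to 11%.

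The reach has limits. The child moderation models are described with an interaction between parenting and the child's markers rather than condition. In comparisons of twins within a family, an intervener effect common to both twins cancels.

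**What to change.** In the primary model and the child-outcome models, add a random intervener effect on the post-intervention condition effect, in the intervention arm only, with small-sample degrees of freedom (for example Kenward-Roger). Make this the primary model, or at least a prespecified sensitivity analysis reported next to it. Record which intervener visited each family: the adherence logs are a natural place, but the article does not say that they hold this. Report the number of interveners, their caseloads and the estimated ICC. State who makes the control calls, so that the nesting is clear.

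The cost is one variance term and no new participants or visits, but the loss of precision can be more than slight. At 10 interveners and ICC .02 there are about 22 degrees of freedom, and the interval is 1.047 × 2.07/1.96 = 1.11 times as wide. At 5 interveners and ICC .05 there are about 7, and the factor is 1.229 × 2.34/1.96 = 1.47. A variance estimated from five interveners is also imprecise, which is a fair reason to prefer the sensitivity analysis if the team is that small.

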## Abbreviations

DTI, diffusion tensor imaging; L-CID, Leiden consortium on individual development; RCT, Randomized controlled trial; SDQ, Strengths and difficulties questionnaire; VIPP-CC, Video-feedback intervention to promote positive parenting – child care; VIPP-SD, Video-feedback intervention to promote positive parenting and sensitive discipline; VIPP-Twins, Video-feedback intervention to promote positive parenting – twin families.
